**Process measures:**

In both intervention groups ('BOFT+' and the 'Healthy toddler') process characteristics of the interventions will be measured additionally by brief questionnaires for parents and for YHC professionals regarding each of the intervention elements, as developed in prior projects of the research group. Adherence to the distinct elements of the Prevention-program will be registered by the YHC-team. The process measures include:

- \*\* Adherence to the distinct elements of the intervention (YHC Professionals), using form completed directly after the contact.
- \*\* Appreciation/satisfaction regarding the interventions (YHC professionals and parents) with regard to the distinct elements. (Mangunkusumo et al., 2007).
- \*\* Description of additional time investment (and appreciation) by YHC-professionals and parents.

**Measures regarding the Cost-effectiveness evaluation:**

With regard to the costs of the 'BOFT+'- and the 'Healthy toddler' intervention, we will assess the costs of additional time of YHC contacts, training of YHC-personnel, other program costs (e.g. material costs; non-client related time investments of YHC-personnel with respect to the intervention package). Data on time investments, expenditures and program costs will be collected by questionnaires among YHC-personnel and parents (see Process evaluation), and from YHC administrative data sources.

**PROCEDURE OF THE STUDY****Training of the YHC professionals in the two intervention groups**

Before the start of both interventions, the YHC professionals (generally the YHC-nurses and YHC-physicians) belonging to the 2 intervention groups, will be trained to apply the 'BOFT+' respectively the 'Healthy toddler' intervention.

**Training regarding the 'BOFT+' intervention:**

The team of the well-baby clinic usually consists of one doctor and a one or two Youth Health Care nurses. The 15 'BOFT+' intervention teams will be trained before start of the study. The training consists of 2 sessions of 4 hours each. During the course of the project (from start of inclusion to the final intervention in the study will take circa 2 1/2 to 3 years), 'booster' sessions will be planned every six months to motivate the 'BOFT+' intervention teams and to ensure proper compliance to the protocol of the intervention. Every training will be focused on another age group, but exactly the same principles from the learning theory will be used.

**Training regarding the 'Healthy toddler' intervention:**

During a full-day session prior to the start of the 'Healthy toddler' intervention and a half-day 'booster' session 4 months after the start of the intervention in order to rehearse the trained skills, YHC professionals will be trained in using the motivational interviewing in the context of the YHC-Overweight prevention protocol. This training will be given by a professional, certified trainer of motivational interviewing techniques as applied in (preventive) health care in cooperation with the Knowledge Center for Overweight (Kenniscentrum Overgewicht). Training will be in small groups including circa 10-15 YHC professionals.

According to the general principles of motivational interviewing, the following elements will be included in the training in order to enhance self-management by parents regarding their parenting style and parenting practices concerning improvement of the four energy balance-related behaviors:

Stimulation of making parents aware of the risk for overweight and its potential adverse effect for their child. Stimulation of favorable change of parental attitudes and motivations regarding overweight prevention and authoritative parenting. Stimulation of the parents perception of being responsible for the health of their child. Stimulation goal setting and providing feed-back in the context of realistic goals that may increase authoritative parenting and improve energy balance-related behaviors in their child. Providing information on beneficial parental practices and stimulating to teach parents these skills. Providing information in order to find specific information when parents have specific questions regarding parenting or overweight prevention.

**Numbers of parents/children included in the study**

A total of 45 YHC-teams of circa ten regional services providing Youth Health Care, will participate in the study. We assume, on average, 15 toddlers per age group per month per YHC-team to be scheduled for a regular visit at a certain age (i.e. 2 weeks after birth at the start of the inclusion procedure). In the course of an inclusion period of maximally 12 months in the project, the 45 participating YHC-teams together will have invited a total of 3.000 parents/toddlers in the study (two intervention groups and one control group).

Taking into account informed consent by 50% and dropout between baseline and follow-up of 30%, we expect complete data from a total of 1.050 parents/toddlers at follow-up, equally divided over the control group and the two intervention groups.

**Information about the study, informed consent, invitation to participate, baseline measurements**

All parents of the children in the study population will, circa 2 weeks after birth, during a regular home visit by the YHC-nurse be informed about the study and will be invited to participate; this can be discussed at and informed consent can be given at the first regular visit to the YHC-center at age of circa one month old. Parents receive information about the study; informed consent form; and a brief questionnaire with items on background data (see above; data gathering at T0).

***Intervention group (a): 'BOFT+'***

Parents that are allocated to a 'BOFT+' YHC-team will receive care during the regularly scheduled visits. However their YHC-professionals will be trained according to the 'BOFT+' principles and the content of child rearing advices will be influenced by those principles; at certain contact moments specific supporting materials will be offered to the parents (see above and see 'BOFT+' annex).

***Intervention group (b): the 'Healthy toddler'***

In case of the 'Healthy toddler' intervention group, parents will also receive care during the regularly scheduled visits. However, one month prior to the visit at child age 18 months, these parents will receive an invitation to visit the 'Healthy toddler' website to obtain tailored information prior to the YHC-visit. Parents can participate via Internet or by completing a paper assessment questionnaire that should be sent back by mail. Parents completing the Internet version will receive tailored feedback immediately. Parents completing the paper version will be mailed a paper version of the tailored advice.

Parents that are allocated to a 'Healthy toddler' intervention YHC-team will be offered a 18-month visit that is 15 minutes longer than a regular visit and that includes face-to-face counseling based on motivational interviewing. During the counseling the parents can discuss any issue that arose from the tailored feedback.

Circa one month after the face-to-face counseling, these parents will receive a reminder by email or by mailed letter, including the tailored advice.

At child age of circa 24 months, circa one month before the next regular visit to the YHC center, the parents in this group will again receive a request to complete the 'Healthy toddler' assessment by Internet or via paper, and receive tailored feedback. The feedback can be discussed during the YHC-visit that will be allowed 10 minutes extra time for face-to-face counseling based on motivational interviewing. Circa one month after the face-to-face counseling, these parents will receive a reminder by email or by mailed letter, including the tailored advice.

## 7. STATISTICAL ANALYSIS

### **Intervention effect:**

To assess the intervention effect, multilevel analyses will be applied to allow for dependency between the individual measurements within the randomized YHC-teams (Campbell et al., 2004). The multilevel approach is also appropriate for the analyses regarding longitudinal data in the study. Multilevel linear regression analyses will be conducted for the continuous outcome variables with group (intervention or control) as independent variable and baseline values and potential confounders as covariates. Multilevel logistic regression will be performed in case of dichotomous outcome variables.

Additionally, effect modification by gender, parental educational level, ethnicity, and parental overweight status will be conducted by introducing an interaction term into the regression analyses. If this interaction term reaches statistical significance, stratified analyses will be carried out.

### **Mediation of the effect:**

We will conduct a mediation analyses in order to verify whether parenting styles and practices can explain the achieved intervention effect regarding energy balance-related behaviors. Mediation of the intervention effect by important process measures will additionally be assessed (Mangunkusumo et al., 2007). Analyses will be conducted according suggestions by Baron et al. (1986) using multilevel regression analyses and structural equation modeling.

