## 6. METHODS

### MEASUREMENTS AND OUTCOME MEASURES

Given informed consent, data will be collected from the YHC-files of the participating families/children; parent-questionnaires to be completed at home; registration forms to be completed by YHC-professionals at the end of distinct YHC-contact moments (mainly process information); brief assessment forms to be completed by parents after distinct YHC-contact moments (process information). Anthropometrical measures (length, weight; waist circumference from age 24 months on) will be recorded according to standardized YHC protocols at the YHC-centers.

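### Mediation by process measures is planned, but these are collected only in the intervention arms, so a mediated share against usual care cannot be validly read from them

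*Protocol*

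**What the plan says.** Section 7 of the protocol plans two mediation analyses. The first asks whether parenting styles and practices explain the effect on the energy balance-related behaviours. The second is stated in one sentence: "Mediation of the intervention effect by important process measures will additionally be assessed". For both, the protocol cites the 1986 paper on moderators and mediators (the causal-steps approach) and names multilevel regression and structural equation modelling.

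Section 6 (Process measures) says where the process data come from: "In both intervention groups ('BOFT+' and the 'Healthy toddler') process characteristics of the interventions will be measured additionally by brief questionnaires for parents". Professionals complete such questionnaires as well. The listed items concern the interventions themselves:

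- for adherence, "Adherence to the distinct elements of the intervention (YHC Professionals), using form completed directly after the contact"
- extra time invested on either side, by staff and by families
- for appreciation, "Appreciation/satisfaction regarding the interventions (YHC professionals and parents) with regard to the distinct elements".

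The opening paragraph of Section 6 also lists registration forms for professionals and "brief assessment forms to be completed by parents after distinct YHC-contact moments (process information"), without naming arms.

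The parenting questionnaires are listed at T2 (15 months) and T3 (36 months) with no arm restriction. Healthy toddler is delivered at about 18 and 24 months.

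**The concern.** Mediation of a randomised contrast needs a mediator that can take a value in both arms being compared. One path runs from arm to mediator, and the other from mediator to outcome given arm. Followed as written, the plan has no process data in usual care, so the first path has nothing to compare.

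If adherence is set to zero in controls, the software will still return a mediated share. The information on the second path then comes only from comparing more with less adherent families inside an intervention arm. Families that follow the programme closely may well differ in motivation, education or circumstances that also bear on play, breakfast, drinks and TV time.

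At stake is a statement that adherence to, or satisfaction with, the programme explains its effect, when the data cannot distinguish that from selection. Which arms complete which forms is settled at the data-collection stage, so a later analysis plan could not create the missing control values.

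**Working it through.** The protocol gives no figure for this point, so nothing is reproduced. The check is of what the design can estimate.

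**1. Data available.** Expected complete data: 1,050 families over three arms, 1,050 / 3 = 350 per arm (Section 4, Power considerations). Control families with planned process measures: 0 of about 350.

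**2. Mediator left missing in controls.** Write A for arm (0 usual care, 1 intervention), M for the process measure and Y for the outcome. The steps need M regressed on A, and Y regressed on A and M. Among families with M recorded, A is always 1, so the columns [1, A, M] have rank 2 of 3. Neither the A-to-M path nor the effect of A given M can be estimated.

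**3. Adherence set to zero in controls.** The model can now be fitted. M does not vary in controls, and A absorbs the shift between arms, so the slope on M comes only from the intervention arm. Let Y = c·A + b·M + γ·U + error, with U an unmeasured trait such as motivation. In the intervention arm let M = μ + λ·U + τ·noise, with U, the noise and the error all of unit variance. The fitted slope is then

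b* = b + γλ / (λ² + τ²), and the apparent indirect effect is b*·μ.

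The following values are assumptions for illustration and are not in the protocol: μ = 0.6, λ = 0.15, τ = 0.2, total effect 0.40. Then λ² + τ² = 0.0225 + 0.0400 = 0.0625, and the excess indirect effect is γ × 0.15 / 0.0625 × 0.6 = 1.44γ:

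- γ = 0: excess 0
- γ = 0.1: excess 0.144
- γ = 0.3: excess 0.432

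A simulation of 200,000 families with the same values, and adherence held between 0 and 1, agrees closely:

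| Case | True indirect | Fitted indirect | Fitted direct | Total |
|---|---|---|---|---|
| No confounder, half mediated | 0.20 | 0.200 | 0.202 | 0.402 |
| γ = 0.3, none mediated | 0 | 0.453 | −0.056 | 0.397 |
| γ = 0.3, half mediated | 0.20 | 0.655 | −0.264 | 0.391 |

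In the second row the whole effect appears mediated although none of it is.

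**4. Appreciation.** Step 3 has no counterpart here. A family that was not offered the programme does not have zero satisfaction with it. The value is undefined.

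**5. Timing of the parenting mediators.** These are planned without an arm restriction, so steps 1 to 4 do not apply. The sequence for Healthy toddler is:

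- 15 months: parenting scales (T2)
- about 18 and 24 months: intervention
- 24 months: weight, length and waist only
- 36 months: parenting scales and behavioural outcomes together (T3).

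At the planned ages, the only parenting measure after the intervention is taken at the same time as the outcome, so the order of change cannot be shown. BOFT+ starts from birth, so for that arm T2 lies between start and outcome, although contacts continue to 24 months.

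**The case against.** The strongest reply is that zero is a real value for adherence in usual care, because those families are not offered the elements, and that the zero-filled model returns the truth (0.200) when there is no confounding. That stands. It is why the point is that the result cannot be validly read as mediation, and not that no number can be produced. Confounding of mediator and outcome is a limitation of any mediation analysis. Here, however, the arm-to-mediator path is also fixed by construction, so randomised variation contributes nothing to the mediator-outcome slope.

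Adjustment can help in part. Parental attitudes and motivation are measured at T2, which precedes Healthy toddler at the planned ages. For BOFT+ the same measure comes after the start of the intervention and is not a baseline covariate.

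It is also true that the general paragraph of Section 6 names no arms, and that the choice and coding of process measures could be left to an analysis plan. But the more specific paragraph places the measures in the intervention groups, and nothing extends them to usual care.

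A reader might infer that the cost comparison with usual care has the same gap, since "Data on time investments, expenditures and program costs will be collected by questionnaires among YHC-personnel and parents (see Process evaluation"). The documents do not support that. The cost paragraph counts what the interventions add, which is zero in usual care by definition. It also draws on administrative data with no arm restriction. The added visit time for Healthy toddler is fixed at 15 and 10 minutes. What remains is narrow: BOFT+ is given within regular visits with no stated extra minutes, so the usual-care time against which its additional time is judged should be stated.

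**Conclusion.** The concern holds for mediation by process measures. As written, the plan gives about 350 control families no value of the mediator. Any mediated share would need adherence to be zero-filled, and would rest on non-randomised differences within an intervention arm. The size of the error is unknown. Under the illustrative values it runs from 0 with no confounding to about 0.45 at γ = 0.3, which exceeds the total effect of about 0.40.

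This rests on reading the Process measures paragraph as limiting collection to the two intervention arms, which is its plain sense.

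A reader might also infer that all the planned mediation fails. It does not: the parenting analysis can be estimated against usual care, and only its interpretation for Healthy toddler is limited by timing. The primary outcomes, the effect models and the sample size are not touched. The change is worth making because it is nearly free and prevents an unsupported explanatory claim.

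**What to change.** In Section 7, Mediation of the effect:

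- Replace mediation by process measures with an exploratory association of adherence with outcome within each intervention arm, allowing for clustering by team and adjusting for measured parental characteristics. State that it does not show that adherence explains the effect.
- Keep satisfaction descriptive, as Section 7 (Descriptive analyses of process measures) already provides.
- For parenting mediators, estimate the indirect effect as a product of coefficients (arm to mediator, times mediator to outcome given arm) with a confidence interval. State which measurement wave is used. Label the Healthy toddler result concurrent and exploratory.

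In Section 6, cost-effectiveness measures, add one sentence naming the usual-care time reference for the additional contact time of BOFT+.

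An adherence-adjusted estimate with randomised arm as instrument is not a simple substitute. It also sets control adherence to zero, and it assumes that allocation acts only through recorded adherence. That is doubtful for BOFT+, where trained nurses shape the advice at all regular visits.

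The cost is a few sentences and no new data. The trial gives up a mediation claim for process measures.

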### **Descriptive analyses of process measures:**

Adherence to and satisfaction with the distinct elements of the 'BOFT+' and the 'Healthy toddler' interventions by parents and professionals will be described. We will explore YHC-center characteristics and parent/toddler characteristics that are associated with the degree of adherence and satisfaction using multiple linear or logistic regression analyses.

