**POWER CONSIDERATIONS AND DETECTABLE DIFFERENCES**

We expect to receive complete data of 1.050 parents/toddlers at follow up at age 36 months old, equally divided over the 2 intervention groups and the control group. We assume equal standard deviations in the intervention groups and the control group, alpha of 0.05 and power of 0.80. We applied a correction factor to account for the cluster design, assuming an average cluster size of 23,3 toddlers (1.050/45) and an intra-class correlation coefficient of 0.10. For this expected sample size and assumptions, we calculated minimal detectable differences between an intervention and the control group at follow-up. We applied standard deviations and proportions/percentages reported in the literature or currently available data from the prior ZonMw projects (# 50-50140-98; # 4010.0033).

Target behaviors at age 36 months old:

Regarding the mean number of the reported minutes of physical activities of the children per day at age 36 months old, the study can detect a difference between intervention/control group of 18 minutes/day (SD=52 min/day). Regarding the mean consumption of sugar-sweetened drinks in glasses per day, a difference of 0.5 glasses/day (SD=1.5 glasses/day) can be detected. Regarding the mean number of minutes of TV viewing per day, a difference of 11 minutes/day can be detected (SD=32 minutes/day).

BMI at age 36 months old:

A difference of 0.44 BMI points between the mean BMI in the intervention group and the mean BMI in the control group at age 36 months can be detected by the study (SD=1.3) (Atkin & Davies, 2000).

Since we will use repeated measures (at age 15 months respectively 24 months in addition to 36 months) as covariates in the analyses, the power will be higher than indicated, which will facilitate the exploration of interaction effects of child gender, social disadvantage, ethnic background, and parental overweight status.

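### Ordinary regression of adherence and satisfaction on YHC-center characteristics ignores clustering by team, so intervals for center-level associations will be too narrow where records are per family or contact

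*Protocol*

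**What the plan says.** Section 7 of the protocol has three regression-based parts that bear on this point.

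- **Intervention effect:** "multilevel analyses will be applied to allow for dependency between the individual measurements within the randomized YHC-teams". Multilevel linear or logistic models are named for continuous and dichotomous outcomes.
- **Mediation of the effect**, including mediation by process measures: "using multilevel regression analyses and structural equation modeling".
- **Descriptive analyses of process measures:** the plan is to explore "YHC-center characteristics and parent/toddler characteristics that are associated with the degree of adherence and satisfaction using multiple linear or logistic regression analyses". No multilevel term appears here.

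The process measures are defined in section 6. They are collected in the two intervention groups only. Professionals record adherence on a form directly after the contact, and satisfaction is collected from both professionals and parents. Section 4 puts 15 teams in each intervention group, so process data come from at most 30 teams.

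**The concern.** A center characteristic takes a single value for all families served by a team. The information about its association with adherence therefore comes from at most 30 units, or 15 if each intervention is modelled separately, which is plausible because the intervention elements differ. Ordinary regression on family-level records would treat that information as coming from about 700 completers (30 × 23.3) or 1,000 enrolled families (30 × 33.3).

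The protocol recognises this dependency for the effect analysis. It uses multilevel models when process measures are mediators, but not when they are the outcome, and it gives no reason for the difference.

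Process evaluation is one of the three study questions. At stake is whether reported associations between center features and adherence or satisfaction carry honest uncertainty.

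**Working it through.** **Inputs**

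- Correlation and cluster size, from the power section: "assuming an average cluster size of 23,3 toddlers (1.050/45) and an intra-class correlation coefficient of 0.10".
- Enrolled families per team, from the time schedule: 500 per arm / 15 teams = 33.3.
- Teams with process data: 2 × 15 = 30 (sections 4 and 6).
- Professionals per team: one doctor and one or two nurses (section 6, BOFT+ training), taken as 2.5.
- Intra-class correlation of adherence or satisfaction: not given. The value 0.10 is borrowed from the trial outcomes and varied below.

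**Step 1. Reproduce the plan's own cluster correction.** The protocol gives no error rate for the process analysis, but its detectable differences rest on a design effect that can be checked.

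DEFF = 1 + (m − 1) × ICC = 1 + 22.33 × 0.10 = 3.23. With 350 per arm, the effective n is 350 / 3.233 = 108.2. The detectable difference is (z_alpha + z_power) × SD × √(2 / 108.2). With one-sided alpha 0.05 and power 0.80 the multiplier is 0.338 SD, which gives 17.6, 0.51, 10.8 and 0.439. These round to the stated 18 min, 0.5 glasses, 11 min and 0.44 BMI points. Two-sided alpha gives 19.8, 0.57, 12.2 and 0.495, which do not match. Sidedness is a separate matter; what counts here is that a design effect of 3.23 is the protocol's own.

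**Step 2. Center-level predictor, one record per family, ICC 0.10.** Ordinary regression understates the standard error by a factor of √DEFF. The true size of a nominal two-sided 5% test is 2 × [1 − Φ(1.96 / √DEFF)].

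- m = 23.3: DEFF 3.23, √DEFF 1.80, true size 27.6%
- m = 33.3: DEFF 4.23, √DEFF 2.06, true size 34.1%

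In terms of intervals, a nominal 95% interval has 1/1.80 = 56% or 1/2.06 = 49% of its proper width, and covers in about 72.4% or 65.9% of cases.

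**Step 3. Range over the unknown correlation.**

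| Assumed ICC | True size, m = 23.3 | True size, m = 33.3 |
|---|---|---|
| 0.01 | 7.6% | 8.8% |
| 0.02 | 10.3% | 12.7% |
| 0.05 | 17.8% | 22.6% |
| 0.10 | 27.6% | 34.1% |
| 0.15 | 34.7% | 41.8% |
| 0.20 | 40.2% | 47.3% |

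No return rate for process forms is stated. With only 10 or 15 records per team and ICC 0.10, the size would be 15.5% or 20.6%.

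**Step 4. The rest of the sentence.**

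- Parent/toddler characteristics: DEFF is approximately 1 + (m − 1) × ICC_x × ICC_y. With ICC_y = 0.10 the size is 5% if the covariate is not clustered, and 7.6% (m = 23.3) or 8.8% (m = 33.3) if ICC_x = 0.10. Only a markedly clustered covariate (assumed ICC_x = 0.30) takes it to 12.9% or 16.3%.
- Satisfaction recorded once per professional: m = 2.5, DEFF = 1 + 1.5 × 0.10 = 1.15, size 6.8%.

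**Step 5. Simulation check.** A linear model was simulated with a null team-level covariate (binary or continuous), 15 or 30 teams, 23 or 33 families per team, and 4,000 runs per setting. At ICC 0.10, ordinary regression rejected in 26.7% to 34.9% of runs. Regression on one mean per team rejected in 4.3% to 5.7% across all settings and all ICCs simulated (0.02, 0.05 and 0.10). The logistic model was not simulated.

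**The case against.** The strongest reply is that this analysis is headed descriptive, is worded as exploration, and has no hypothesis, significance level or decision rule. The "alpha of 0.05 and power of 0.80" belongs to the power calculation for trial outcomes. That is correct, and an error rate quoted against 5% supplies a test that the protocol does not state. It does not remove the problem, because the same understatement affects any reported confidence interval.

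The inputs are also borrowed. The correlation of 0.10 is planned for the 36-month outcomes, 23.3 counts completers at that age, and 33.3 presumes a record for every enrolled family. This stands, and the figures must be read as conditional.

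The unit of analysis is not stated either. If adherence were summarised once per team, ordinary regression on center characteristics would be valid. This also stands, so the point is limited to family-level or contact-level records.

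Finally, model detail for an exploratory analysis may be left to an analysis plan that is not shown. Here, however, the protocol names a model class itself, and the neighbouring paragraphs name a different one.

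A reader might infer four stronger things that the document does not support:

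- **That adherence is more strongly clustered than 0.10.** The protocol gives no figure for it.
- **That the same one or two nurses deliver and record everything in a team.** The team includes a doctor, and parents in the Healthy toddler arm complete the E-health module themselves.
- **That the question of to whom the elements are applied is distorted to the same degree.** That question concerns parent and toddler characteristics, where inflation is small (step 4).
- **That implementation will be misdirected.** Nothing in the protocol ties implementation to a test result here.

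**Conclusion.** The point holds in limited form. For center-level characteristics analysed on family-level or contact-level records, the named model gives intervals that are too narrow. With one record per family, the protocol's planning correlation of 0.10 and 23.3 to 33.3 families per team, standard errors are too small by a factor of 1.80 to 2.06, and a nominal 5% test has a true size of 27.6% to 34.1%. The size exceeds 5% at every correlation examined (0.01 to 0.20), but how far depends on a value the protocol does not give for process measures.

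The conclusion assumes roughly equal team sizes. Records per contact would put more observations in each team; that case was not quantified.

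This is a modest wording correction to a secondary, exploratory analysis. The primary comparison and the mediation analysis already use multilevel models and are unaffected.

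**What to change.** In section 7, under the descriptive analyses of process measures, name multilevel linear or logistic regression with a random team intercept. State that center characteristics enter at team level and are tested on team-level degrees of freedom. If models are fitted separately by intervention, and 15 teams make the multilevel logistic model unstable, use a team-level summary analysis for the center characteristics instead. It would also help to state whether the record is per contact, per family, per professional or per team.

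The cost is one or two sentences. No new data are needed, and the model class is already in the plan. The price is wider intervals for center-level associations, and with 15 teams per intervention only strong associations will be distinguishable from chance.
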